### Statistical procedures

For data comparison between pre-exercise and post-exercise and across groups, nonparametric (Spearman’s correlation (ρ), chi-square test (χ^2^), and Mann–Whitney U test), and parametric tests (t-test, analysis of variance (ANOVA), multivariate analysis of variance (MANOVA), multivariate linear regression, and canonical discriminant analysis) will be used depending on the variable studied, as well as *post hoc* tests (Duncan and Waller-Duncan - ANOVA and MANOVA) [49]. The significance level will be set at 0.05. All statistical analysis will be performed using SPSS version 22.0.

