### Baseline assessment of subjects

After recruitment, the subjects will undergo baseline assessment to collect information on their main characteristics before intervention. A descriptive exploratory questionnaire will be administered to collect information on i) demographic and socioeconomic variables (gender, age, socioeconomic status, education, skin color and marital status); ii) behavioral variables (physical activity measured by the International Physical Activity Questionnaire (www.ipaq.ki.se), smoking status, and alcohol consumption); iii) anthropometric variables (body weight, height, and waist circumference); iv) clinical variables (BP and use of antihypertensive medication); and v) quality of life assessed by the Medical Outcomes Study 36-Item Short Form Health Survey (SF-36) [42]. Eligible individuals who are willing to participate will be instructed to fast for 8 h and come for a scheduled second visit at the study site. In this visit, subjects will have blood samples collected for blood testing, in addition to the assessment of FMD of the brachial artery and ambulatory blood pressure monitoring (ABPM) cuff placement. A snack will be offered at the end of this visit. In the third visit, the ABPM cuff will be removed and subjects will undergo physical fitness tests (VO_2_max). In the fourth visit, 1-RM testing will be conducted. Subjects who did not show up for the scheduled visits will be contacted again. All blood samples will be collected by a nurse technician. All assessment procedures will be supervised by the study investigators and ICFUC medical staff.

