### Assessment of flow-mediated dilation (FMD)

Endothelial function will be measured noninvasively by using brachial artery ultrasound (EnVisor series, Philips Ultrasound, Bothell, WA, USA). This assessment will be performed with a 7 to 12 MHz linear transducer in a heated room at 21 to 24 °C at ICFUC. A software program will be used for two-dimensional color-Doppler imaging acquisition with a simultaneously recorded electrocardiogram (ECG). Image data will be recorded on a DVD. To minimize operational errors, the subject’s arm, and the ultrasound transducer will be positioned and maintained in the same position during the procedure. Baseline images will be recorded. A cuff will be placed around the forearm and inflated to 50 mmHg above systolic pressure for at least 5 min and then removed. Longitudinal ultrasound images of the brachial artery walls will be acquired to assess endothelium-dependent vasodilation. The expected coefficient of variation between the images will be 1.8 to 5.0 %. Flow-dependent vasodilation responses will be expressed as the percentage change in the brachial diameter [36].

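### The plan names no baseline-adjusted comparison of FMD between arms, and its only rank test of outcome levels, Mann–Whitney U, suits neither paired nor three-arm data

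*Protocol article*

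**What the plan says.** The Statistical procedures section of the protocol article opens "For data comparison between pre-exercise and post-exercise and across groups" and then lists procedures for both purposes together.

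- The nonparametric entries are Spearman's correlation, chi-square "and Mann–Whitney U test".
- The parametric entries begin "t-test, analysis of variance (ANOVA), multivariate analysis of variance (MANOVA" and end "multivariate linear regression, and canonical discriminant analysis) will be used depending on the variable studied".
- The post hoc procedures are tied to the parametric models: "tests (Duncan and Waller-Duncan - ANOVA and MANOVA".
- On the error rate: "The significance level will be set at 0.05".

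No test is assigned to FMD or to any other outcome. ANCOVA, Kruskal–Wallis, Wilcoxon signed-rank and Friedman are not named.

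Baseline values exist. The Baseline assessment section has blood drawn at the second visit, "in addition to the assessment of FMD of the brachial artery". The FMD section defines the measure: "Flow-dependent vasodilation responses will be expressed as the percentage change in the brachial diameter". That is a change within one ultrasound session, so it does not itself adjust for the pre-training visit. The Randomization procedure section sets three equal arms of 27. Table 1 gives FMD, endothelial progenitor cells (EPCs) and endothelial microparticles as the subjects of the primary objectives.

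**The concern.** There are two linked points.

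First, the natural between-arm question is how week-12 FMD differs by arm for subjects with the same starting FMD. The plan holds the data to answer that, but names no analysis that does so. With 27 per arm the lost precision matters. If the arms were compared on post-training values alone, a chance imbalance in baseline FMD would also enter the contrast.

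Second, if an outcome needs a rank method, the list offers only Mann–Whitney U for comparing levels. That test assumes two independent samples. On pre/post data it ignores the pairing. Across three arms it gives no overall test, only pairwise tests, and the listed post hoc procedures do not cover those because they belong to ANOVA and MANOVA. EPC and microparticle counts, which are primary, may need such a method. The article gives no distribution for them, so skewness is an assumption.

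**Working it through.** **The plan's own figure.** The sample size formula under Sample selection is n = s²/e² × t². With s = 0.05 and e = 0.02, s²/e² = 0.0025/0.0004 = 6.25. Then 6.25 × 2.045² = 26.14 and 6.25 × 2.069² = 26.75, and 3 × 26.75 = 80.26, rounded up to 81. The stated 27 per arm reproduces if 0.05 is read as s and the error as 0.02; the printed notation is a separate matter. This is a one-sample precision calculation with no power and no between-arm effect, so it neither supports nor refutes the present point.

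**Inputs.** From the article: 27 per arm, three arms, level 0.05. Sidedness is not stated in Statistical procedures, but the t values above are two-sided, so two-sided is used. Assumed: pre–post correlation r of 0.3 to 0.7, equal variances before and after, an arm difference or shift of 0.5 SD, and 80 % power for detectable differences.

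**Baseline adjustment.** Relative variance of an arm contrast:
- post-only: 1
- change score: 2(1 − r)
- ANCOVA: 1 − r²

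ANCOVA against post-only is therefore 1 − r², and ANCOVA against change score is (1 − r²)/(2(1 − r)) = (1 + r)/2.

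| r | ANCOVA / post-only | cut | ANCOVA / change | cut |
|---|---|---|---|---|
| 0.3 | 0.91 | 9 % | 0.65 | 35 % |
| 0.5 | 0.75 | 25 % | 0.75 | 25 % |
| 0.7 | 0.51 | 49 % | 0.85 | 15 % |

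At r = 0.5, 27/0.75 = 36, so 27 per arm behaves like 36.

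The pairwise detectable difference in SD units is √v × (1.960 + 0.842) × √(2/27), where v is the relative variance. For v = 1 this is 2.802 × 0.272 = 0.762. Power is by normal approximation.

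| r | detectable difference: post / change / ANCOVA | power at 0.5 SD: post / change / ANCOVA |
|---|---|---|
| 0.3 | 0.762 / 0.902 / 0.727 | 45 / 34 / 49 % |
| 0.5 | 0.762 / 0.762 / 0.660 | 45 / 45 / 56 % |
| 0.7 | 0.762 / 0.591 / 0.545 | 45 / 66 / 73 % |

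**Mann–Whitney on paired data.** Simulation of 20,000 normal samples of 27 pairs, two-sided 0.05:

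| r | type I error, Mann–Whitney | power at 0.5 SD shift, Mann–Whitney | power, signed-rank |
|---|---|---|---|
| 0.3 | 1.9 % | 41 % | 55 % |
| 0.5 | 0.7 % | 39 % | 69 % |
| 0.7 | 0.1 % | 37 % | 88 % |

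Signed-rank held its level, at 4.7–4.9 %.

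**Mann–Whitney across three arms.** Three independent tests at 0.05 would give 1 − 0.95³ = 14.3 % familywise error. The three comparisons share arms, and simulation (20,000 runs, 27 per arm, no true difference) gives 12.0 %. One Kruskal–Wallis test gives 4.8 %.

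**The case against.** A reader might infer that the arms will be compared with no adjustment at all and that baseline FMD is thrown away. The article does not support either reading. It never says the comparisons are unadjusted. The listed linear regression could carry arm and baseline together. The pre/post comparison uses baseline by construction. The t-test and ANOVA have paired, change-score and repeated-measures forms, and nothing restricts the between-arm test to post-training values. In a randomised trial the post-only, change-score and ANCOVA contrasts all estimate the arm effect without bias, so what ANCOVA adds is precision. A condensed article may also leave the model for each endpoint to a fuller document. All of this stands, and it limits the first point to a recommendation.

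A reader might also infer that Mann–Whitney has been assigned to paired data or to the cell counts. It has not. It sits in a pooled list chosen by variable, next to Spearman and chi-square, which do not compare pre/post levels of a continuous outcome either. If it were applied to positively correlated pairs it would be conservative: power is lost, but false positives do not increase. This also stands, and it makes the harm conditional.

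What the objection does not remove is that Mann–Whitney has no paired or three-sample form. The appeal to families of tests therefore fails for the one rank test of levels that the plan names.

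**Conclusion.** The point holds in limited form. The plan names no baseline-adjusted between-arm analysis for FMD, and the regression it lists has no stated role. The one rank test of levels it names fits neither the pairing nor an overall comparison of three arms.

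The precision at stake is worth having at this sample size, but its amount rests on an assumed correlation, for which the article gives no value. The variance formulas also ignore the small cost of estimating the baseline slope. The rank-test figures assume normal data and apply only if Mann–Whitney is actually used in those ways. The inflation to about 12 % is the only one of these effects that would raise false positives, and it needs three uncorrected pairwise tests.

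This is an improvement available at no cost. It is not a defect that invalidates the trial.

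**What to change.** In Statistical procedures, make these changes:

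- Name the primary comparison: ANCOVA of week-12 FMD % on arm, with baseline FMD % as covariate, reporting the three adjusted pairwise differences with 95 % confidence intervals.
- Apply the same baseline-adjusted model to EPC and microparticle counts, log-transformed if they prove skewed.
- Where a rank method is needed, replace Mann–Whitney as the stand-alone test with Kruskal–Wallis across arms, followed by multiplicity-adjusted pairwise tests, and with Wilcoxon signed-rank for pre/post.
- State that within-arm pre/post tests are descriptive.

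The cost is wording only. Baseline FMD and blood samples are already scheduled, no extra subjects or visits are needed, and the methods are available in the SPSS version named. The article gives the trial status as recruiting, so the wording can be settled before outcome data are complete.

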**Methods/design:**

Eighty-one subjects with SAH aged 18 to 70 years will be selected and randomly assigned to three types of exercise training: AT, RT or CT. The study will involve the following procedures and tests: anamnesis, anthropometric assessment, echocardiography, blood pressure measurements through ambulatory blood pressure monitoring, flow-mediated dilation, ergospirometry, one repetition maximum test (1-RM), and blood collection (number of circulating endothelial progenitor cells, number of circulating endothelial microparticles, lipid profile, glucose, glycated hemoglobin, and creatinine). The AT intervention will consist of a 40-min exercise session with progressive intensities ranging from 50 to 75 % of heart rate reserve. The RT intervention will consist of a 40-minute session with four sets of six to 12 repetitions with a rest period of 60 to 90 seconds between each set and each type of exercise. Weight loads will be adjusted to 60 to 80 % of 1-RM for six types of exercise. The CT intervention will consist of a 20-min aerobic exercise session, followed by an additional 20-min resistance exercise session; each resistance exercise will have two sets less to match the total training volume.

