where, n_po_ = sample size at time point zero, s^2^ = variance of the sampling distribution, and t_α;gl_ = sampling distribution according to a predetermined error probability (*P* ≤ 0.05) and degrees of freedom for n_po_.

The mean incidence rate of SAH in Brazil is 20 % of the population [40]. Considering the baseline value (n_0_ = 30); t_α;gl_ = t_0.05;29_ = 2.045; s^2^ = 0.05 (based on the maximum value of the coefficient of variation of endothelial vasodilation); and the maximum error of the estimate taken as the maximum variability in arterial diameter measures by two observers (0.02 %) [41], it was estimated that n_p1_ = 26.1 ≅ 26 hypertensive individuals. Thus, in the estimate of *n,* the approximation used considered n_p1_ = 26, gl = 23, and t_0.05;23_ = 2.069. The n_p1_ = 26.8 ≅ 27. The estimate of the sample size for the study was *n* = 80.3 ≅ 81 hypertensive individuals who will be randomly assigned to the three training interventions.

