### Randomization procedure

A randomization for the proposed interventions will be generated by a computer program (www.randomization.org) including the distribution coded at a 1:1 ratio. The random assignment of subjects to training intervention groups will be into three blocks of 27. Subjects will be drawn up to 27 in each intervention group: aerobic training (AT), resistance training (RT), and combined training (CT, resistance and aerobic). All subjects will be blinded to intervention allocation and will have access to this information only after the baseline assessment. All evaluators of the study subjects will be also blinded to intervention allocation.

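### The two named post hoc tests, Duncan and Waller-Duncan, have no stated F gate and no deciding rule, so 0.05 is not secured across the three arm comparisons

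*Protocol article*

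**What the plan says.** Participants are "randomly assigned to three types of exercise training: AT, RT or CT" (Abstract, Methods/design), which gives three pairwise comparisons. The Randomization procedure section fixes the arm size: "Subjects will be drawn up to 27 in each intervention group".

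The Statistical procedures section lists nonparametric and parametric methods, ANOVA and MANOVA among them, to be chosen according to the variable. It then names the follow-up "tests (Duncan and Waller-Duncan - ANOVA and MANOVA" and adds "The significance level will be set at 0.05".

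The section does not state:
- whether 0.05 applies to each comparison or to the three together;
- whether the post hoc tests wait for a significant F;
- which of the two procedures decides if they disagree;
- what loss ratio Waller-Duncan is to use.

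**The concern.** The first primary objective (Table 1) concerns the effects of the three training types on flow-mediated dilation. A claim that one type does better than another will come from the post hoc tests, so their error rate is the error rate of that conclusion.

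Duncan's test relaxes its level as more means are spanned. Waller-Duncan takes no alpha at all: its user chooses how much worse a false positive is than a missed difference. Setting 0.05 therefore does not by itself fix the chance of a false claim among the three arms. The two procedures can also group the same means differently.

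**Working it through.** **Inputs.** From the article: three arms, 27 per arm, level 0.05. Error degrees of freedom are 3 × (27 − 1) = 78 if everyone is analysed. Assumed: normal outcomes with equal variance, and k = 100 for Waller-Duncan. SD means the within-arm standard deviation.

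**The plan's own arm size.** With s = 0.05 and error 0.02, s²/e² = 0.0025/0.0004 = 6.25. Then 6.25 × 2.045² = 26.1 and 6.25 × 2.069² = 26.8. Three times the unrounded 26.755 is 80.3, rounded up to 81. This reproduces the article. (The article writes 0.05 as the variance, whereas the arithmetic uses it as the SD. That does not affect this point.)

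**Duncan.** The level for a range of p means is 1 − (1 − 0.05)^(p−1). For p = 2 this is 0.05; for p = 3 it is 1 − 0.95² = 0.0975. The critical studentised ranges at 78 df are 2.815 for p = 2 and 2.962 for p = 3. Tukey uses 3.379 for every pair. Without a gate and with all arms equal, a false claim occurs exactly when the full range exceeds 2.962, so the familywise error is 9.75 %.

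**Waller-Duncan.** The critical t depends on the observed F. It was solved numerically from the k-ratio Bayes rule with 2 and 78 df. As a check, in large samples with F = 4 the solution is 1.988, against the closed form 1.72 × √(4/3) = 1.986. With k = 100, the critical t is 2.118 at F = 3.11 (the 5 % point of F), 1.793 at F = 25 and 1.764 at F = 100. The ordinary 5 % value is 1.991, so the test becomes more lenient than 5 % once F is large.

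**Simulation.** Each case used 500,000 trials with 27 per arm. The figure is the chance of at least one false claim among truly equal arms.

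| Procedure | All equal | One arm differs by 0.8 / 1.2 / 2.0 SD |
|---|---|---|
| Duncan, no gate | 9.7 % | 5.0 / 5.0 / 5.0 % |
| Duncan, after significant F | 5.0 % | 5.0 / 5.0 / 5.0 % |
| Waller-Duncan (k = 100), no gate | 8.1 % | 6.0 / 7.1 / 7.9 % |
| Waller-Duncan (k = 100), after significant F | 5.0 % | 6.0 / 7.1 / 7.9 % |
| Pairwise t, after significant F | 5.0 % | 5.0 / 5.0 / 5.0 % |
| Tukey | 4.9 % | 1.9 / 2.0 / 1.9 % |

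When one arm differs by only 0.3 or 0.5 SD, ungated Duncan gives 4.5 % and 4.8 %, and ungated Waller-Duncan gives 4.0 % and 4.7 %.

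**Range over k.** The same calculation, ungated with all arms equal, gives 14.6 % for k = 50, 8.1 % for k = 100 and 1.9 % for k = 500. With the gate and one arm differing by 0.8 to 2.0 SD, it gives 10.3 to 13.0 %, 6.0 to 7.9 % and 1.6 to 2.3 % respectively. The error rate follows k, not the stated 0.05.

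**Why a gate is enough for three arms.** If all arms are equal, a false claim first needs a false significant F, which has probability 5 %. If exactly one arm differs, only one pair is truly equal, and it is tested at 5 %. No other configuration contains a true null pair. This argument fails for Waller-Duncan because its critical value falls below the 5 % value at large F.

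**The case against.** The strongest defence is that post hoc normally means after a significant F, and that the article attaches these tests to ANOVA and MANOVA. A condensed article may leave the gate to a fuller plan. On that reading Duncan holds 5 % for three arms. This stands, so the 9.7 % must be stated as conditional on there being no gate.

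Second, the article does not call 0.05 familywise. Per comparison, ungated Duncan does hold it: a given equal pair is declared different in 4.1 % of trials with all arms equal, and in 5.0 % when the third arm differs by 0.8 or 2 SD. This also stands. The familywise reading is the natural one for a post hoc procedure over three arms, but it is a reading.

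Neither defence rescues Waller-Duncan. It has no alpha to which 0.05 could apply, and with k = 100 it exceeds 5 % even with the gate when one arm differs by 0.8 to 2.0 SD.

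A reader might infer three stronger things that the document does not support:
- **Both tests run at about twice the stated error.** That is true only of ungated Duncan, familywise, with all arms equal.
- **The article is at fault for giving no confidence intervals.** Reporting format is commonly left to a fuller plan, and other listed methods (t-test, ANOVA, regression) yield estimates with standard errors.
- **The choice between the two tests will be made after seeing the results.** The article does not rule this out, but it does not say so.

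**Conclusion.** The point holds in conditional form. As written, the section names two procedures and one level, and does not tie them together.

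Read familywise, Duncan misses 0.05 only without the gate and only when all arms are equal (about 9.7 %). Waller-Duncan is the firmer part of the point, because 0.05 does not govern it on either reading. Its size rests on the assumed k = 100: about 8 % ungated with all arms equal, and about 6 to 8 % gated with one arm 0.8 to 2.0 SD away. A large k such as 500 would instead make it stricter than 5 %.

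The figures assume all 81 participants are analysed, with normal outcomes and equal variances. Multiplicity over the several primary outcomes (dilation, progenitor cells, microparticles) is a separate matter and is not counted. The change is worth making because pairwise claims are central to the trial and the cost is very small.

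**What to change.** Drop Waller-Duncan and prespecify, before any unblinded analysis, one alpha-indexed procedure for the three pairwise comparisons. Either of these will do:

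1. Test the arm effect with the planned ANOVA F at 0.05, and make the three pairwise comparisons only if it is significant. This holds the familywise error at 5 % for exactly three arms. Duncan kept behind the same gate would also hold 5 %, if the gate is written down.
2. Use Tukey or Holm with no gate.

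State that 0.05 applies across the three comparisons. Preferably, report each arm difference with its 95 % confidence interval. Tukey gives simultaneous intervals, whereas the intervals from option 1 are per comparison.

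The cost is one sentence in the statistical section, with no change to design or sample size. Option 2 loses a little power: with 27 per arm, Tukey needs an observed difference of 3.379/√27 = 0.650 SD. Duncan needs 2.815/√27 = 0.542 SD for adjacent means and 2.962/√27 = 0.570 SD for the extremes. Option 1 keeps the pairwise threshold at 0.542 SD once the F is significant.

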### Ethical issues

The study protocol followed the principles of the Declaration of Helsinki and was approved by the research ethics committee (Protocol 925.406 by Instituto de Cardiologia do RS/Fundação Universitária de Cardiologia – Brazil, dated 22 December 2014 and signed by [name] [name]). Furthermore, all subjects will read and give their informed consent for participation in the research study. All information will be confidential, subjects’ names will be kept confidential, and data will be collected for academic purposes only according to Resolution CNS N1466/12 [50]. If subjects in the RT and CT groups do not show any improvements of endothelial function (primary endpoint) or BP levels compared to those in the AT group, they will be offered the opportunity to practice the AT protocol after completion of the study to ensure equal benefits for all subjects.

## Discussion

The Study of Endothelial Function Response to Exercise Training (SEFRET) is a single-site study that will be conducted in the city of Porto Alegre, Brazil. The study will be conducted in accordance with the principles of Good Clinical Practice and all requirements established by ICFUC relevant bodies and collaborators.

The study results are expected to provide evidence of cardiovascular protective effects of different types of exercise training by modulating endothelial function in individuals with SAH. Knowing the magnitude of improvement of endothelium-dependent vasodilation by different types of exercise training can provide scientific evidence to the prescription of exercise programs for vascular protection targeted to hypertensive individuals. An adequate exercise program can lead to significant changes in cardiovascular function and promote health benefits and BP control, thus reducing adverse cardiovascular outcomes.

